Following prescreening assessment of basic eligibility criteria (e.g., maternal age, singleton pregnancy, admission to labor ward, interest in study participation), potentially eligible women provide written informed consent in their preferred language. Before signing, a participant must demonstrate that she fully understands the information in the informed consent form by successfully completing a comprehension assessment. Participants provide separate consent for long-term storage of biological samples (detailed below) for possible future research testing not defined in the LABOR Study protocol. Participants may choose not to have these specimens stored for possible future research testing or withdraw their consent for long-term specimen storage at any time and remain in the study.

Study nurses collect information from consented participants about relevant maternal demographics, health and risk behaviors, and medical and obstetrical history in fixed case report forms. Research staff review the participant’s medical records to abstract relevant antenatal care, medical comorbidities, prior ultrasound findings, and key laboratory results performed during pregnancy and in the hospital prior to study enrollment. LABOR Study staff perform a physical examination and collect peripheral blood, urine, and vaginal/rectal swabs for real-time testing and storage (
Table 1).

**Table 1. T1:** Schedule of evaluations.

	Enrollment	Labor	Delivery	Before discharge	7 days after delivery	42 days after delivery
Informed consent	•					
Collection / review of locator information	•			•	•	•
Medical chart abstraction	•	•	•	•		
Demographic / behavioral assessment	•					
Maternal physical exam	•					
Ultrasound	•					
Maternal / fetal sensor placement	•					
Labor progress assessments		•				
Maternal / fetal sensor removal				•		
Maternal and fetal / neonatal outcomes assessment		•	•	•	•	•
Neonatal physical exam				•		
Maternal point-of-care tests (HIV, syphilis, hemoglobin, urinalysis)	•					
Maternal chemistry	•					
Maternal hematology	•			•		
Maternal lactate	•					
Cord blood lactate			•			
Neonatal blood culture (if NICU admission)				•		
Maternal vaginal / rectal swabs storage	•					
Maternal blood storage	•			•		
Maternal urine storage	•					
Cord blood storage			•			
Neonatal DBS card storage				•		
Neonatal urine storage (if moderate or severe encephalopathy)				•		

NICU, neonatal intensive care unit; DBS, dried blood spot

**
*Sensor placement*
**

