Throughout labor, delivery, and immediately postpartum, the scribes are responsible for recording detailed information about all actions performed, medications provided, and diagnoses made for each participant. Scribes document all actions carried out either by clinical staff or the participant herself, which may include assessments (e.g., cervical examination), procedures (e.g., amniotomy), or events (e.g., maternal pushing). Information recorded about medications administered includes name, route of administration, dose, and time administered. Scribes document all diagnoses made by on-site clinical care providers throughout labor, delivery, and immediately postpartum. Finally, they are responsible for ensuring continuous data collection from all study sensors and documenting any adjustments or interruptions.

During delivery and immediately postpartum, scribes are encouraged to prioritize real-time documentation of time and mode of delivery, time of cord clamping and placental delivery, estimated blood loss measured by a study-supplied calibrated drape (for vaginal deliveries), and any delivery complications. If scribes are present for cesarean delivery, they are additionally responsible for documenting the time and type of skin and uterine incisions. After delivery, scribes document neonatal vital status, Apgar scores, sex, birth weight, head circumference, and provision of any positive pressure ventilation.

Immediately after the umbilical cord is clamped and cut, a sample of umbilical venous blood is drawn and tested for lactate concentration on a point-of-care platform. Additional venous cord blood is also processed and stored for future testing.

**
*Postpartum maternal and neonatal procedures*
**

After transfer from the labor ward, LABOR Study staff closely track mother-infant pairs, visit each participant at least daily, and perform abstraction of maternal and neonatal medical charts. Study staff document maternal postpartum care, neonatal care, and final maternal and neonatal outcomes prior to hospital discharge. An additional maternal blood sample is collected once the mother is stabilized following transfer from the delivery room for immediate hematology analysis and storage for future testing.

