### Data analysis and statistical plan

**
*Study outcomes*
**

The primary outcomes of the LABOR Study include a composite maternal outcome of potentially actionable incident adverse events and a composite fetal / neonatal outcome of the same nature (
Table 2). Secondary outcomes include the individual components of the two primary composite outcomes: maternal outcomes including maternal death, incident intrapartum hemorrhage, postpartum hemorrhage, incident hypertensive disorders (eclampsia, severe preeclampsia, preeclampsia, superimposed preeclampsia, severe gestational hypertension), and incident maternal infection (intrauterine inflammation or infection, endometritis), and fetal / neonatal outcomes including intrapartum stillbirth, neonatal death, encephalopathy, and sepsis. The LABOR Study distinguishes between prevalent conditions (those present at the time of enrollment) and incident conditions (those arising after enrollment). Although we identify and assess frequency of prevalent conditions, the primary focus of analytic approaches described below is the characterization and prediction of incident conditions.

**Table 2. T2:** Study outcome definitions.

Maternal Outcomes	
Maternal death	Death of a maternal participant after study enrollment and up to 42 days postpartum, irrespective of cause
Incident intrapartum hemorrhage	Intrapartum vaginal bleeding of ≥ 1000 mL of blood prior to delivery of the placenta
Postpartum hemorrhage	Blood loss of ≥ 1000 mL or any bleeding leading to an adverse event, regardless of mode of delivery, either within the 24 hours after delivery of the placenta (primary) or up to 42 days postpartum (secondary)
Incident eclampsia	New onset of tonic-clonic, focal, or multi-focal seizures in the absence of other causative conditions
Incident severe preeclampsia	New development of systolic blood pressure ≥ 140 mmHg or diastolic pressure ≥ 90 mmHg measured at least 4 hours apart in addition to proteinuria and at least one of the following severe features: thrombocytopenia, renal insufficiency, impaired liver function, pulmonary edema, new-onset cerebral or visual disturbances, or rise in systolic blood pressure to ≥ 160 mmHg or diastolic pressure to ≥ 110 mmHg
Incident preeclampsia	New development of systolic blood pressure ≥140 mmHg or diastolic pressure ≥ 90 mmHg measured at least 4 hours apart in addition to proteinuria in the absence of severe features described above

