Incident superimposed preeclampsia	New development of preeclampsia as defined above in a woman with chronic hypertension
Incident severe gestational hypertension	New development of severe range blood pressure (i.e., ≥ 160 mmHg systolic pressure or ≥ 110 mmHg diastolic pressure) without proteinuria, thrombocytopenia, renal insufficiency, impaired liver function, pulmonary edema, or cerebral or visual disturbances
Incident intrauterine inflammation or infection	Maternal fever and any of the following prior to delivery: fetal tachycardia, maternal leukocytosis, drainage of purulent fluid from cervical os
Endometritis	Presence of two or more of the following on any 2 of the first 10 days postpartum, exclusive of the first 24 hours and with no other recognized cause: maternal fever, abdominal pain, uterine tenderness, purulent drainage from uterus
Fetal / Neonatal Outcomes	
Intrapartum stillbirth	A stillborn fetus weighing at least 500g meeting all of the following criteria at birth: no heart rate, no respirations, absence of pulsation of the umbilical cord, and no definitive movement of voluntary muscles, and in which fetal heart tones were documented on the ultrasound performed at the time of LABOR Study enrollment
Neonatal death	Death of a live-born neonate within 28 days of birth
Neonatal encephalopathy	Live-born neonate weighing at least 1500g that meets one of the following four physiologic criteria: venous cord lactate > 7 mmol/L; 10 minute APGAR < 5; continued need for ventilation at ≥ 10 minutes of life; intrapartum hemorrhage, cord prolapse, severe fetal heart rate abnormality, or uterine rupture, and that demonstrates moderately or severely abnormal neurologic findings in at least three of the following six categories: spontaneous activity, posture, level of consciousness, tone, primitive reflexes, autonomic nervous system.
Neonatal sepsis	Live-born neonate exhibiting one or more signs of early-onset sepsis (i.e., convulsions, tachypnea, severe chest indrawing, nasal flaring, grunting, bulging fontanelle, pus draining from ear, umbilical redness extending to the skin, fever, low body temperature, many or severe skin pustules, lethargy / unconsciousness, or less than normal movement) with a positive blood culture (excluding contaminants) within the first seven days of life

**
*Sample size*
**

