*Descriptive analysis of baseline, intrapartum, and outcome variables.* Common methods for descriptive statistics will be used to examine the distribution of key baseline factors, intrapartum events, and overall outcomes in the study population (e.g., frequencies for categorical variables and measures of centrality and dispersion for quantitative variables). These methods will also be used to examine unadjusted (crude) differences in the distribution of outcomes and intrapartum events by baseline factors. Key baseline factors will include maternal demographics, medical history and obstetrical risk factors, enrollment ultrasound, physical examination and laboratory values collected at admission or enrollment in the study. Intrapartum events will include time-varying variables related to the course of labor (e.g., cervical examinations), provider interventions (e.g., drugs, procedures), and continuous monitoring through fetal and maternal sensors.

*Associations between baseline variables, interventions, and outcomes.* Generalized linear models will be used to estimate the adjusted relative risk with 95% confidence interval of outcomes associated with baseline factors. Covariates (baseline factors) for inclusion in the multivariable models will be identified
*a priori* based on clinical relevance and using causal directed acyclic graphs. We will start by fitting two separate models for binary outcome variables (yes/no) for the composite maternal and fetal / neonatal outcomes, respectively. If baseline factors of interest are found to be associated with the composite outcomes, we will fit models to each of the individual outcome components within each composite (maternal or fetal / neonatal). A similar modeling approach to that used for the composite and individual outcomes will be used to estimate associations between baseline factors (covariates) and key intrapartum interventions such as cesarean delivery.

*Predictive models and risk stratification.* We will develop and validate models to use baseline variables to predict the probability of each outcome. These predicted probabilities can be used to stratify patients by risk. Because of the expected high dimensionality of the data, we will consider the use of dimension reduction techniques such as deep learning autoencoders
^
17

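### Enrollment laboratory values can complete the definition of an incident maternal outcome and also serve as its predictors, so part of their association with infection and preeclampsia is built in

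*Protocol article*

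**What the plan says.** **Incidence.** Under Study outcomes: "The LABOR Study distinguishes between prevalent conditions (those present at the time of enrollment) and incident conditions (those arising after enrollment"). The section makes incident conditions the main analytic focus.

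**Definitions (Table 2).**
- The intrauterine infection outcome is defined as "Maternal fever and any of the following prior to delivery: fetal tachycardia, maternal leukocytosis, drainage of purulent fluid from cervical os". Leukocytosis is one of three alternatives.
- Incident preeclampsia: newly developed blood pressure elevation "measured at least 4 hours apart in addition to proteinuria in the absence of severe features described above". The newness attaches to the pressure. Proteinuria carries no timing.
- Severe preeclampsia adds at least one of "thrombocytopenia, renal insufficiency, impaired liver function, pulmonary edema, new-onset cerebral or visual disturbances", or severe-range pressure.
- Severe gestational hypertension is new severe-range pressure "without proteinuria, thrombocytopenia, renal insufficiency, impaired liver function, pulmonary edema, or cerebral or visual disturbances".

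**Schedule (Table 1 and the postpartum procedures).** The row "Maternal point-of-care tests (HIV, syphilis, hemoglobin, urinalysis") is marked at enrollment only, as is maternal chemistry. Hematology is marked at enrollment and before discharge. The text dates the later sample: "An additional maternal blood sample is collected once the mother is stabilized following transfer from the delivery room for immediate hematology analysis".

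**Analysis.** Key baseline factors include "physical examination and laboratory values collected at admission or enrollment in the study". Adjusted relative risks are to be estimated for baseline factors, and baseline variables are to be used to predict each outcome.

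**The concern.** Read together, these rules let one enrollment result do two jobs. A woman with leukocytosis at enrollment who becomes febrile in labor meets the infection definition at once. A febrile woman with a normal enrollment count needs another sign, or a later count that only routine care would order. The same holds for new hypertension with and without enrollment proteinuria. If the enrollment value is then a covariate or a feature in the model for that outcome, some of its relative risk or importance reflects the case definition rather than biology.

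Cross-validation cannot reveal this, because every fold uses the same outcome definition. The choice of covariates by causal graph is described for the association models, not for the prediction models. The study's products are risk algorithms and a shared dataset, so the built-in association would be passed on to later users.

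**Working it through.** The article states no figure that depends on this point, so there is none to reproduce. The check sets schedule against definitions, then illustrates size with assumed inputs.

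**Step 1: what is scheduled, and what each result can do.** I assume hematology supplies leukocytes and platelets, chemistry supplies renal and liver results, and urinalysis supplies proteinuria.

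| Result | Scheduled before delivery | Scheduled after delivery | Effect of an enrollment abnormality under Table 2 |
|---|---|---|---|
| Leukocytes | Enrollment | Yes, too late for the pre-delivery criterion | Completes infection once fever occurs |
| Proteinuria | Enrollment | No | Completes preeclampsia once hypertension occurs |
| Platelets | Enrollment | Yes | Moves preeclampsia to severe preeclampsia |
| Renal, liver | Enrollment | No | Moves preeclampsia to severe preeclampsia |

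**Step 2: effect on the maternal composite.**
- New non-severe hypertension: with proteinuria the woman is a preeclampsia case; without it, no listed hypertensive component applies. Enrollment proteinuria can decide composite membership here.
- New severe-range pressure: with proteinuria it is severe preeclampsia; without it, severe gestational hypertension, provided no other listed abnormality is recorded. Both are in the composite.
- Renal, liver or platelet results: with proteinuria they only sort between two components that both count. Without proteinuria an abnormal result excludes the woman from severe gestational hypertension. They never create a composite case.

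**Step 3: size for leukocytosis and infection (all inputs assumed).** Suppose fever after enrollment is unrelated to enrollment leukocytosis, and an enrollment leukocytosis is accepted as the criterion. Among febrile women let q be the probability of another listed sign, r the probability of new leukocytosis, and c the probability that routine care tests for it and it is recorded. Then

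RR = 1 / [1 − (1 − q)(1 − rc)].

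For q = 0.2 to 0.8 and r = 0.2 to 0.5:
- c = 0: from 1/0.8 = 1.25 to 1/0.2 = 5.0.
- c = 0.5: from 1/(1 − 0.2 × 0.75) = 1.18 to 1/(1 − 0.8 × 0.9) = 3.57.
- c = 1: from 1/(1 − 0.2 × 0.5) = 1.11 to 1/(1 − 0.8 × 0.8) = 2.78.

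Even complete capture leaves a ratio above 1, because the woman with enrollment leukocytosis has already met the second criterion.

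**Step 4: case capture.** With L the share with enrollment leukocytosis, and carried-forward cases counted as true,

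sensitivity = [L + (1 − L)(1 − (1 − q)(1 − rc))] / [L + (1 − L)(1 − (1 − q)(1 − r))].

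Example: L = 0.1, q = 0.2, r = 0.5, c = 0 gives (0.1 + 0.9 × 0.2)/(0.1 + 0.9 × 0.6) = 0.28/0.64 = 0.44. Over L = 0.1 to 0.3 and the ranges above, sensitivity is 0.44 to 0.97 at c = 0, 0.72 to 0.98 at c = 0.5, and 1.0 at c = 1.

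**Step 5: proteinuria and preeclampsia.** If a share t of women with new hypertension and no enrollment proteinuria are retested and found positive, RR = 1/t: 10, 5 and 2.5 for t = 10%, 20% and 40% (assumed), with no effect of proteinuria on hypertension.

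**Step 6: dilution.** If the composite also arises by unrelated routes with risk b, and f is the risk of fever, then, ignoring overlap, the composite ratio is (b + f)/(b + f/RR). This lies between 1 and the component ratio and approaches 1 as b grows.

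**The case against.** A reader might infer that laboratory changes arising after enrollment are missed. The article does not support that. Table 1 marks chart abstraction in labor, at delivery and before discharge. Scribes record provider diagnoses, and the discharge review reconciles laboratory tests from labor onward. What stands is narrower: these changes are found only where routine care looked, which may differ by site and clinical suspicion.

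It can also be said that no text tells sites to carry an enrollment result forward, and that sources and windows usually sit in the full protocol or analysis plan. That is fair about practice. But Table 2 as worded admits the enrollment value, and incidence is stated for conditions, not for each criterion. The overlap follows from the stated rules.

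Three further points stand as limits:
- Fetal tachycardia and purulent drainage need no laboratory test, and fetal ECG is recorded from enrollment. New thrombocytopenia can appear in the postpartum sample.
- No future information leaks into prediction: the fever or hypertension still lies ahead when the laboratory value is known. Proteinuria is also part of the disease, so no effect on hypertension is not the same as no effect on preeclampsia.
- Association models for components are fitted only if the composite shows an association. The prediction models carry no such condition.

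**Conclusion.** The point holds for component outcomes. Enrollment leukocytosis can complete incident infection, enrollment proteinuria can complete incident preeclampsia, and enrollment platelet, renal or liver results can move a case into severe preeclampsia. Where the same values are predictors, their association is partly built in.

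For the maternal composite the effect is diluted. It comes mainly through leukocytosis with fever and proteinuria with non-severe new hypertension. A reader might infer that chemistry associations with the composite are inflated too; Table 2 rules this out, since chemistry only re-sorts cases or excludes them.

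The ratios above are not estimates for this study. They rest on assumed shares and on fever or hypertension being unrelated to the enrollment value. The highest values for leukocytosis set later chart capture to zero. The direction is firm under those assumptions; the size depends on routine retesting, which the article does not quantify. This is a worthwhile, inexpensive improvement to the analysis, not a flaw that invalidates the outcomes.

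**What to change.** Follow-up ended in September 2022, so the change is to derivation and reporting.

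1. Keep the Table 2 outcomes as primary. For each case, flag whether the qualifying laboratory result predates the fever or hypertension.
2. For the infection, preeclampsia and maternal composite models that use enrollment leukocyte count or urinalysis, and for severe preeclampsia models that use enrollment platelets or chemistry, also report (a) the model without those predictors and (b) the model with an outcome version that omits the laboratory element: new fever, or new hypertension.

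Restricting the primary outcome to samples dated at or after onset is not recommended. It would discard the only pre-delivery tests scheduled for everyone and leave laboratory confirmation before delivery to clinician-ordered tests.

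Cost: additional model runs on existing data, and possibly less favourable reported performance for laboratory-based predictors.

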## Methods

### Study design

The LABOR Study is a multi-country, prospective, observational cohort study. It was initially designed to enroll a maximum of 15,000 mother-infant pairs but this figure was modified to 12,000 after recruitment was slowed by the SARS-CoV-2 pandemic at all sites. The study has been registered prospectively with clinicaltrials.gov under identifier NCT04102644 and with the Clinical Trial Registry of India under CTRI/2020/01/022589.

Women are screened for study participation at the time of presentation to the hospital for delivery and followed for 42 days after delivery. The study’s co-primary outcomes are composites of incident maternal and fetal or neonatal adverse events that may be attributed to the intrapartum period. For the mother, the primary composite outcome includes death, hemorrhage, hypertensive disorders, or infection. For the fetus/newborn the primary composite outcome includes intrapartum stillbirth, neonatal death, encephalopathy, or sepsis. The LABOR Study has been designed following the guidelines outlined by the Strengthening the Reporting of Observational Studies in Epidemiology (STROBE) statement (
Figure 1)
^
7
^.

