Trained and certified study providers perform up to two neurological examinations to diagnose intrapartum-related neonatal encephalopathy for newborns weighing at least 1500 grams who meet any one of the following four physiologic criteria: ten-minute Apgar score <5, continued need for positive pressure ventilation at ten minutes of life, venous cord blood lactate >7mmol/L, or acute perinatal event, defined as intrapartum hemorrhage, umbilical cord prolapse, fetal distress as evidenced by an abnormal heart rate or pattern, or uterine rupture. The newborn neurological examination is based the modified Sarnat examination that evaluates level of consciousness, spontaneous movement, posture, tone, primitive reflexes, and the autonomic nervous system
^
12,
13
^. For all newborns diagnosed with either moderate or severe encephalopathy by neurological examination, urine specimens are collected and stored for future testing. One urine specimen is collected on the second day of life and another on day seven of life or discharge, whichever occurs first.

All newborns admitted to the neonatal intensive care unit within the first seven days of life are assessed for signs or symptoms of sepsis, and a blood culture is obtained (prior to antibiotics, if administered). Repeat blood cultures may be collected in cases of new, worsening, or recurrent signs or symptoms of sepsis during the first seven days of life. LABOR Study staff collect a dried blood spot card on all study newborns at 24 hours after delivery or discharge, whichever occurs first, to be stored for future analyses.

At discharge, LABOR Study staff complete a final review of the maternal and neonatal hospital course and reconcile key study diagnoses, medications, laboratory and radiographic diagnostic tests, and other interventions that occurred during labor, delivery, and the inpatient postpartum period. Study staff are responsible for confirming or correcting data recorded by scribes during the intrapartum and immediate postpartum periods and for adding any additional diagnoses and/or interventions that have occurred since delivery as documented in the medical record or in study chart notes. Finally, study staff categorize birth outcomes according to a modified rubric to assign a clinical delivery phenotype
^
14
^.

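### The encephalopathy definition requires an examination finding, so a newborn who meets a physiologic criterion but dies unexamined cannot be a case in the encephalopathy models

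*Protocol article*

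**What the plan says.** Table 2 (Data analysis and statistical plan) limits neonatal encephalopathy to live-born neonates of at least 1500 g. Two things are required: one of four physiologic criteria, and a newborn that "demonstrates moderately or severely abnormal neurologic findings in at least three of the following six categories". There is no alternative route to the diagnosis.

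The postpartum part of Study procedures describes the source of that finding: "Trained and certified study providers perform up to two neurological examinations". It gives no rule for a newborn who dies before the first examination.

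Neonatal death is a separate component, defined as "Death of a live-born neonate within 28 days of birth". Under Study design, "For the fetus/newborn the primary composite outcome includes intrapartum stillbirth, neonatal death, encephalopathy, or sepsis".

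The Statistical analysis section then goes below the composite. Where baseline factors are associated with a composite, "we will fit models to each of the individual outcome components within each composite". Separately, and without that condition, it plans "models to use baseline variables to predict the probability of each outcome". The Missing data paragraph considers imputation or weighting when more than 20% of participants have missing data, and reports complete-case analyses alongside.

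**The concern.** The encephalopathy outcome can be observed only in newborns who survive long enough to be examined. Those with a lethal insult may die first. Death then removes true cases from the encephalopathy outcome, and does so more often for any factor that makes the insult more severe.

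Two results are at stake. Predicted probabilities from the encephalopathy model would be too low on the absolute scale. Relative risks for factors linked to early death would be pulled toward 1. Both matter because the study's stated purpose is to stratify women and fetuses prospectively by risk.

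**Working it through.** The plan gives no figure on this point, so there is none to reproduce. The inputs below marked as assumed are not in the documents.

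**Inputs**
- Cohort: 12,000 (Sample size section), taken as roughly the number of live births (assumed).
- True encephalopathy risk *p*: 1% to 3% (assumed).
- Share *f* of true cases who die unexamined: 5% to 30% (assumed).
- True relative risk: 2.0, from risks of 2.667% in the exposed and 1.333% in the unexposed, which average 2% with equal groups (assumed).

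**Step 1: absolute risk.** If unexamined deaths are coded no, the observed risk is *p*(1 − *f*). If they are excluded, it is *p*(1 − *f*)/(1 − *pf*). At *p* = 2% and *f* = 20% there are 240 true cases, of whom 48 die unexamined and 192 are observed.
- Coded no: 192/12,000 = 1.600%.
- Excluded: 192/(12,000 − 48) = 1.606%.

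At *p* = 2%, coding as no gives 1.90%, 1.80%, 1.60% and 1.40% for *f* = 5%, 10%, 20% and 30%.

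**Step 2: relative risk.** If coded no, the observed ratio is 2.0 × (1 − *f* exposed)/(1 − *f* unexposed). If excluded, each risk is also divided by 1 − *pf* for its own group.

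| *f* exposed | *f* unexposed | coded no | excluded |
|---|---|---|---|
| 20% | 20% | 2.00 | 2.01 |
| 20% | 10% | 2.0 × 0.80/0.90 = 1.78 | 1.79 |
| 30% | 10% | 2.0 × 0.70/0.90 = 1.56 | 1.57 |

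The direction depends on which group has the larger share. With 10% in the exposed and 20% in the unexposed, the ratio would be 2.0 × 0.90/0.80 = 2.25.

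**Step 3: would the missing-data rule catch it?** Unexamined true cases are *pf* of the cohort: from 1% × 5% = 0.05% to 3% × 30% = 0.90%, or 6 to 108 newborns in 12,000. The trigger is more than 20%, which is 2,400. Even if every true case died unexamined, the figure would be at most 3%. The complete-case analysis is the excluded column above.

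**Step 4: is the error visible elsewhere?** In the 20% against 10% scenario, death before examination among affected newborns is 2.667% × 0.20 = 0.53% in the exposed and 1.333% × 0.10 = 0.13% in the unexposed, a ratio of 4.0. The death model would therefore carry a strong signal for the same factor.

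**The case against.** The strongest reply is that the article never says how an unexamined death is coded. The yes/no wording in the Statistical analysis section is attached to the two composite models. Such a death could be coded no, set to missing, excluded or treated as a competing event, and a full analysis plan, not shown here, may settle it. That stands as far as it goes: a reader might infer that the plan counts these newborns as non-cases, but it does not say so. It does not dispose of the point. The outcome definition is fixed in Table 2, the two simplest codings give almost the same error, and the stated missing-data trigger would not be reached by these deaths.

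The second reply is that these newborns are not lost to the study. They are cases in the co-primary composite and in the neonatal death outcome, and the component association models run only after an association with the composite. This also stands. It limits the point to the encephalopathy models.

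The third reply is that nobody knows how many newborns die unexamined, and with equal shares the relative risk is essentially unbiased. That is correct, and is why only a range is given.

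**Conclusion.** The point holds for the encephalopathy association and prediction models, and not for the co-primary composite. Risk is understated in proportion to the share of true cases who die unexamined: 2.00% becomes 1.60% if that share is 20%. A true relative risk of 2.0 becomes 1.78 or 1.56 under the two unequal scenarios and is essentially unchanged when the shares are equal. All of this rests on assumed shares and on those who died unexamined being true cases.

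Four stronger readings are not supported:
- **That the model would give low predicted risk to those in most danger, or reverse an association.** With 10% unexamined among the unexposed, reaching a ratio of 1 needs 2.0 × (1 − *f*) = 0.90, so *f* = 55% in the exposed. At 20% against 10% the exposed still have the higher observed encephalopathy risk: 2.667% × 0.80 = 2.13% against 1.333% × 0.90 = 1.20%.
- **That intrapartum stillbirths are misclassified.** The definition is confined to live-born neonates, and stillbirth is its own component with a 500 g threshold. Merging the two would change the question being asked.
- **That sepsis needs the same recoding.** It does require signs "with a positive blood culture (excluding contaminants) within the first seven days of life", but a culture drawn before death still counts, so only uncultured newborns are affected. Signs are described as assessed in one group: "All newborns admitted to the neonatal intensive care unit within the first seven days of life are assessed for signs or symptoms of sepsis". The listed signs, such as lethargy and reduced movement, also overlap with encephalopathy.
- **That the deaths before assessment are known to be numerous.** The article gives no count.

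**What to change.** Keep the Table 2 definition and report it as planned. For the encephalopathy association and prediction models, also fit a supplementary outcome: encephalopathy, or death before any neurological examination, in a live-born newborn of at least 1500 g who meets at least one of the four physiologic criteria. Report the number who died unexamined, overall and by the main exposures. Table 2 counts none of these deaths and the supplementary outcome counts all of them, so the two together show how far the results depend on their classification.

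Do not add intrapartum stillbirth to this outcome. For sepsis, report only the number who died by day 7 without a culture.

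The cost is a short addition to the analysis text and one further model per analysis. Follow-up is complete, and the article describes collection of vital status, birth weight, Apgar scores, positive pressure ventilation, cord lactate and delivery complications, so no new data are needed. The drawback is a somewhat less cause-specific outcome, because some who died unexamined would not have been encephalopathy cases. The Table 2 result therefore stays beside it.
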